### Data Analysis

The proportional increase of patients referred as a result of the intervention compared with baseline data will be calculated. Change in knowledge of health personnel will be assessed with pre- and postassessment questionnaires prepared using Public Health Foundation of India’s “Certificate Course in Evidence Based Management of Diabetic Retinopathy assessment questionnaire” as a guide (Multimedia Appendix 5). The first 5 questions will be on DM and its complications and the remaining 5 questions will be specific to DR. The Diabetic Retinopathy Awareness Index will be calculated based on the scoring made by Datti et al [9].

Information on DR and duration of DM will be collected, visual acuity will be measured, and stage of DR will be noted to understand the clinical outcomes. Descriptive analysis for the same will be presented. Information on referred data from the intervention hospital will be extrapolated. Mean and SD will be calculated for the demographic variables. The *Z* test will be applied to determine the number of referrals. Paired *t* test will be used for the change in average knowledge score of health care professionals and a chi-square test will be used for pre–post referrals based on the education and experience of health care professions. Data will be analyzed using Epi Info 7.

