## Methods

### Study Design, Setting, and Participants

This is a nonrandomized, pre- and postintervention study without a control group. The study was performed in REMEH. This study included selected health personnel of Scheer Memorial Hospital (the intervention hospital) who are directly involved in providing health services to patients with DM. A total of 19 health personnel of Scheer Memorial Hospital fit the inclusion criteria (4 physicians, 4 pediatricians, 8 medical officers, and 3 assistants).

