### Sampling Techniques

This involved complete enumerations of all health personnel managing patients with DM in the intervention hospital.

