### Outcome

#### Primary Outcome

This includes change in the proportion of referred patients from Scheer Memorial to REMEH compared with baseline referrals before the intervention.

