### Implementation of Intervention

Ethical approval has been obtained from the Nepal Health Research Council. Written informed consent has been obtained from all participants. All selected health personnel of Scheer will visit REMEH for the health education sessions, which will be implemented once a month for 3 months, lasting an hour during the weekends. The session will begin with a preassessment test to know participants’ baseline knowledge about DR. We will deliver a PowerPoint presentation explaining the burden of DM globally and in Nepal. It will include the effect of uncontrolled DM on eyes and possible damage to the retina, risk of DR, and the preventive measures for the early detection and management of DR to avoid vision loss. We will explain to the participants the contents of educational pamphlets. Lastly, we will present the educational video on DR. At the end of the first session, we will hand over the posters, pamphlets, and referral slips to the participants. We will request all 19 participants to distribute pamphlets to patients, counsel them to have fundus examination, and to use referral slips while referring patients to REMEH. We will provide posters related to DR with a request to display them in the waiting area of Scheer Memorial, and at the end of the intervention, we will conduct a quiz and postintervention assessment of the participants. The intervention plan is outlined in Table 1.

Actions expected from selected health personnel in Scheer Memorial:

Counsel patients with DM to visit REMEH.Use the referral slip while referring patients to REMEH.Handover DR-related pamphlets to patients with DM.Record total cases referred to REMEH in a month.

**Table 1 table1:** The intervention plan with IEC^a^ materials used during each visit.

Visit	Materials	Questionnaire(s)
Pilot	All IEC materials	Pre- and postassessment questionnaires
First	PowerPoint presentations, posters, referral slips	Preassessment questionnaire
Second	Video presentation, pamphlets	—
Third	Refresher of the previous session and a small quiz	Postassessment questionnaire

^a^IEC: information education and communication.

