## Results

The study is expected to be completed in 18 months from the start of the project. The baseline data collection was from June to January 2020 for a period of 8 months. The postintervention data collection was from February to September 2021 for a period of 8 months. The last 2 months are planned for data analysis and report writing. Descriptive analysis will be presented on the demographic variables of the health care professionals, demographic variables of patients, and clinical findings by computing means with SD. The proportion of increase in referral will be calculated by the *Z* test. The change in average knowledge score will be calculated by means and SD. *P* value will be calculated by a paired *t* test. The pre- and postintervention referrals will be determined based on the experience and education of the health care professionals by a chi-square test.

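### The Z test for referrals leaves out month-to-month variation and uneven change among clinicians, so its P value is likely too small and its confidence interval too narrow

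*Protocol article*

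**What the plan says.** The Primary Outcome section defines the endpoint as "change in the proportion of referred patients from Scheer Memorial to REMEH compared with baseline referrals before the intervention". Two places name a test for it, and both name a Z test. In Data Analysis, the Z "test will be applied to determine the number of referrals". In Results, "The proportion of increase in referral will be calculated by the" Z test. Neither place mentions over-dispersion, a robust variance, clustering or time.

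The data structure is given elsewhere in the article:
- Study Design, Setting, and Participants: "A total of 19 health personnel of Scheer Memorial Hospital fit the inclusion criteria".
- Sampling Techniques: "This involved complete enumerations of all health personnel managing patients with DM in the intervention hospital".
- Implementation of Intervention asks these staff to "Record total cases referred to REMEH in a month".
- Results: "The baseline data collection was from June to January 2020 for a period of 8 months" and "The postintervention data collection was from February to September 2021 for a period of 8 months".

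There is one intervention hospital and no control group. For the secondary outcome, the knowledge score, the article plans a paired t test, so there the clinician is the unit of analysis.

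**The concern.** The usual Z test on counts or proportions takes its standard error from the Poisson or binomial formula. That formula is right only if referrals arise independently, at a constant rate within each window. Two features of this design make that doubtful.

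- **Months.** Only June to September fall in both windows. October to January occur only at baseline and February to May only after the intervention. Any variation between months beyond chance adds to the variance of the difference between windows.
- **Clinicians.** The intervention acts on 19 people. If one takes up referring and another drops it, many referrals move together.

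The Z test gives both sources zero variance. At stake is the error rate of the primary comparison: an apparent rise in referrals could be declared significant too often, with an interval that looks more precise than it is.

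**Working it through.** The article states no alpha, sample size, baseline referral count or dispersion, so there is no planned figure to reproduce. I assume two-sided alpha 0.05.

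**Inputs from the article:** 19 clinicians; 8 months in each window.

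**Assumed inputs:** 20 to 100 referrals per window; coefficient of variation (CV) of the underlying rate 0.3 to 0.5, taken either between months or between clinician-by-period units.

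**Formulas.** If N referrals per window are spread over k units whose rates are drawn afresh in each window, the mean per unit is μ = N/k and the variance inflation is φ = 1 + μ·CV². The true type I error of the nominal 5% test is 2·(1 − Φ(1.96/√φ)).

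| Source | N | μ | CV | φ | True type I error |
|---|---|---|---|---|---|
| Month (k = 8) | 20 | 2.5 | 0.3 | 1.225 | 7.7% |
| Month | 100 | 12.5 | 0.3 | 2.125 | 17.9% |
| Month | 20 | 2.5 | 0.5 | 1.625 | 12.4% |
| Month | 100 | 12.5 | 0.5 | 4.125 | 33% |
| Clinician-by-period (k = 19) | 20 | 1.05 | 0.3 | 1.09 | 6.1% |
| Clinician-by-period | 20 | 1.05 | 0.5 | 1.26 | 8.1% |
| Clinician-by-period | 100 | 5.26 | 0.3 | 1.47 | 10.6% |
| Clinician-by-period | 100 | 5.26 | 0.5 | 2.32 | 19.8% |

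Simulation with gamma-Poisson rates and no true effect agrees. With 100 referrals per window and clinician-by-period CV 0.3 and 0.5, it gives 10.4% and 19.6%. With no extra variation it gives about 5%, so the excess comes from the added variance.

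**Proportion version.** This simulation assumes 40 patients per clinician per window and 20% referred.
- Clinician-by-period SD of 0.3 and 0.5 on the logit scale gives 11.6% and 22.8%.
- Month SD of 0.2, 0.3 and 0.5 gives 12.2%, 20.5% and 37.5%.
- Stable clinician differences alone, SD 0.5, 1.0 and 1.5, give 4.6%, 3.6% and 2.4%. The test is then conservative.

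**Which remedy treats which source.** I compared the remedies at 100 referrals per window.
- A quasi-Poisson model of the 8+8 monthly totals restores about 5% under month-to-month variation. Under clinician-by-period variation with CV 0.5 it still gives 17.6%, with a mean estimated dispersion of 1.00. At CV 1.0 it gives 40%, against 43% for the Z test. A clinician's shift is shared by all 8 months of a window, so the scatter between months does not show it.
- A clinician-level paired analysis restores about 5% under clinician-by-period variation. It does not do so under month variation, because a shift common to all clinicians does not show in the differences between them.

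**The case against.** - **The variance is not fixed.** The article does not say how the standard error will be computed. Since totals are recorded monthly, a Z test on monthly means with the observed SD also fits the Data Analysis wording. In simulation that version had a type I error of about 7% for month CV 0.2 to 0.5. This stands as a possibility, but the Results wording about a proportion points to the ordinary test, and the article mentions no other variance.
- **The volume may be low.** The Background describes low screening uptake and a poor referral system. With 20 referrals per window the clinician-by-period inflation is only 6% to 8%. This stands, and is why the range starts at 20.
- **Extra variation is not documented.** COVID-19 restrictions are mentioned only as a threat to attendance at the education sessions. Month-to-month variation in referrals is plausible but not stated. This also stands, so the conclusion is that P is likely too small, not that it certainly is.
- **Two stronger readings are tempting.** A reader might infer that P is too small simply because all referrals come from the same 19 clinicians. It is not: stable differences cancel, and alone they make the unpaired test slightly conservative. A reader might also infer a one-sample test with the baseline count taken as known. The article says only that referrals are compared with baseline, so nothing is built on that reading.

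**Conclusion.** The point holds in a conditional form. The only test named for referrals, read as an ordinary Z test on counts or proportions, omits month-to-month variation and uneven change among clinicians. Its P value is then likely too small and its interval too narrow. Under the assumed counts and CVs, the true error of a nominal 5% test runs from about 6%, a minor matter, to about 33%, a serious one. Which end applies cannot be settled from the article, because it gives neither referral counts nor dispersion.

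The article itself names the Z test as the primary test, so this is not a detail merely left to a fuller plan, although a fuller plan could specify the variance. The change should be made. A better variance does not turn the before-after contrast into a causal one: confounding by calendar time remains without a control group.

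**What to change.** 1. Replace the Z test with a quasi-Poisson or negative binomial model of the 8+8 monthly referral totals. Use t-based inference (16 totals − 2 parameters = 14 degrees of freedom) and report the rate ratio with its 95% CI. Add patients with DM seen as an offset if that count exists for both windows. State that this model covers month-to-month variation only, and check for autocorrelation between months.
2. Where referrals can be attributed to clinicians in both windows, add a paired analysis of each clinician's pre-post change (paired t or Wilcoxon signed-rank). A clinician random intercept alone is no substitute: it models the stable part, which cancels already.
3. State that neither analysis removes calendar-time confounding.

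**Cost.** The text change is a few sentences, and any free package can fit the model if Epi Info 7 cannot. The data may cost more. The number of patients with DM seen is not among the items that staff are asked to record. Referral slips are handed out only at the first session, so they cannot trace baseline referrals to clinicians. The planned chi-square test of pre-post referrals by clinicians' education and experience presupposes some such attribution. If a baseline source for it exists, it should be named and used here. Expect a wider interval and a less favourable P value.

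### The planned chi-square test of pre-post referrals by staff education and experience treats referrals from only 19 clinicians as independent, so its P value is unreliable if clinicians differ in how much they change

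*Protocol article*

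**What the plan says.** The Data Analysis section applies a chi-square test to pre-post "referrals based on the education and experience of health care professions". The Results section repeats the plan: "The pre- and postintervention referrals will be determined based on the experience and education of the health care professionals by a chi-square test". Neither place names the unit counted, the education or experience categories, or any allowance for several referrals by one person.

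The source of the referrals is stated. Under Study Design, Setting, and Participants, "A total of 19 health personnel of Scheer Memorial Hospital fit the inclusion criteria", made up of "4 physicians, 4 pediatricians, 8 medical officers, and 3 assistants". Sampling Techniques describes this as "complete enumerations of all health personnel managing patients with DM in the intervention hospital", so the number cannot be raised within this hospital, and the Discussion says that COVID-19 restrictions could reduce participation. Implementation of Intervention shows that these same people generate the referrals: "We will request all 19 participants to distribute pamphlets to patients, counsel them to have fundus examination, and to use referral slips while referring patients".

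This breakdown is neither the primary outcome (change in the proportion referred) nor the secondary outcome (change in staff knowledge).

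**The concern.** Pearson's chi-square compares the cell counts with the scatter expected from independent events. Referrals by one clinician are not independent in the sense that matters here, because they share that clinician's response to the training. A group of 3 or 4 people can show a large shift because one member took up the referral slips and the others did not. The test would credit that shift to the group's education or experience.

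The plan describes no other test of which kinds of staff change their referring. A spurious difference here would be the study's only inferential statement on that question.

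**Working it through.** **Inputs from the article.** 4 + 4 + 8 + 3 = 19 staff, which reproduces the stated total. Baseline and post-intervention windows are each given as 8 months. No referral count, variance or intracluster correlation (ICC) is given.

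**Assumptions.** The four cadres stand in for the undefined education and experience groups. There are 20, 50 or 100 referrals per window. Variation between clinicians is shown as a range.

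**1. Referrals as the unit (2 periods × 4 groups, 3 degrees of freedom).** Each clinician's expected count in each window is (referrals per window / 19), multiplied by an independent gamma factor with mean 1 and the stated CV. Counts are Poisson and there is no true group difference. The table shows how often the nominal 5% test rejects. Repeat runs agree to within about one percentage point.

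| CV of clinician-by-period factor | 20 referrals | 50 referrals | 100 referrals |
|---|---|---|---|
| 0 | 4–5% | 5% | 5% |
| 0.2 | 5–6% | 7% | 8–9% |
| 0.3 | 6% | 9% | 14% |
| 0.5 | 9% | 18% | 32% |
| 0.75 | not used | 36% | 57% |

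To put the CV on a more familiar scale: on a lognormal approximation, the SD of a clinician's log pre-post ratio is √(2 ln(1 + CV²)).
- CV 0.2: √(2 × 0.0392) = 0.28
- CV 0.5: √(2 × 0.2231) = 0.67
- CV 0.75: √(2 × 0.4463) = 0.94

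**2. Stable volume only.** If clinicians differ in volume (CV 1.0) but all change by the same ratio, the rejection rate is 4–5% at 20, 50 and 100 referrals. A clinician who is simply busier in both periods cancels out of a period-by-group table.

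**3. A second model.** Here the log pre-post rate ratio varies between staff, with 3 to 20 baseline referrals each. The test rejects about 5% of the time at SD 0, 8–39% at SD 0.3 and 17–69% at SD 0.5. A design-effect check, 1 + (m − 1) × ICC with m = 10 and ICC = 0.05, gives 1 + 9 × 0.05 = 1.45. The probability that a chi-square on 3 degrees of freedom exceeds its 5% critical value divided by 1.45 is 14.5%.

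**4. Staff as the unit.** If each person were classified (for example, referrals increased: yes or no), the expected counts at a 50% split would be 4 × 0.5 = 2, 2, 8 × 0.5 = 4 and 3 × 0.5 = 1.5 in each column, all below 5. Over every split from 1/18 to 18/1, 7 or 8 of the 8 cells fall below 5. Collapsing to 2×2 does not cure this, because the largest attainable minimum is 9 × 9 / 19 = 4.26. Even so, exact enumeration puts the true size of the uncorrected test at 3.6–4.6% for the 4×2 table and 1.0–9.0% for the 2×2 splits tried. Power is low: about 44% for 80% versus 40% in an 8 versus 11 split.

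**The case against.** **The size is not established.** The article gives no referral count or variance. At 20 referrals per window, or at CVs of 0.2 or less, inflation is small or absent. This stands. A reader might infer that the test has false-positive rates several times nominal. The document does not support that as a fact; it holds only at the larger assumed variations. Identical change in all 19 clinicians is nonetheless unlikely after an education programme, so the direction is not in doubt.

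**The test is not invalid on every reading.** A reader might infer from the small cells that counting staff makes it fail just as badly. The article defines no clinician-level outcome, the 4/4/8/3 split is by cadre rather than by education or experience, and the actual error rate of such a table is near nominal. The count rule fails for certain, but the practical harm is slight.

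**Active clinicians and caseload.** It is tempting to say that one busy clinician, or unequal diabetes caseloads, would bias the comparison. Stable differences of either kind cancel. Only a change between periods matters.

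**Condensation.** Category definitions and a sparse-cell fallback may sit in a fuller document, so their absence is no finding. The chi-square test itself is stated twice, however, and that choice is the point at issue.

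**Weight.** This is a side analysis in a self-described pilot, and the Discussion makes no claim about which staff benefit most. That limits the importance of the point but does not make the P value sound.

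**Conclusion.** The concern holds in a limited form. On the natural reading, the stated test treats referrals from 19 clinicians as independent and overstates the evidence whenever clinicians differ in their pre-post change. With 50–100 referrals per window, the nominal 5% test would reject about 5% of the time at CV 0, rising to 18–32% at CV 0.5 and 36–57% at CV 0.75. These figures rest on assumed counts and variation and on cadre as the grouping. The mechanism follows from the article; the magnitude does not. Since this is neither the primary nor the secondary outcome, it is a point that should be corrected, not one that threatens the study's main result.

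**What to change.** In both Data Analysis and Results, drop the chi-square P value for this breakdown and report pre and post referral counts by education and experience group descriptively.

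Where referrals can be linked to the referring clinician in both periods, any test should take the clinician as unit: a permutation test on each clinician's change in referral count across groups, or an exact test on a per-clinician classification. It should be labelled exploratory. Use counts rather than rates, because the article does not show that diabetes caseloads per clinician are collected. Linkage at baseline is also uncertain, since referral slips are handed over only at the first session. Without linkage, the descriptive table is all that can be supported.

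The cost is one sentence in each of two sections and the loss of a nominal P value. A clinician-level test on 19 people will have low power, so a null result should not be read as showing no difference between groups.

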### Ethical Approval

The ethical approval for this study has been obtained from the Ethical Review Board of Nepal Health Research Council (ERB Protocol Registration Number # 582/2020P).

## Results

The study is expected to be completed in 18 months from the start of the project. The baseline data collection was from June to January 2020 for a period of 8 months. The postintervention data collection was from February to September 2021 for a period of 8 months. The last 2 months are planned for data analysis and report writing. Descriptive analysis will be presented on the demographic variables of the health care professionals, demographic variables of patients, and clinical findings by computing means with SD. The proportion of increase in referral will be calculated by the *Z* test. The change in average knowledge score will be calculated by means and SD. *P* value will be calculated by a paired *t* test. The pre- and postintervention referrals will be determined based on the experience and education of the health care professionals by a chi-square test.

## Discussion

Our study is a nonrandomized, pre- and postintervention design that focuses on health professionals as stakeholders to increase the referral of DR. The stakeholders will be provided health education to create awareness and knowledge about DR using PowerPoint slides, posters, pamphlets, and referral slips. After the intervention, we hope to see increased referral of patients with DR from the intervention hospital (Scheer Memorial) and better knowledge among health care personnel. Different studies have shown that providing health education sessions on DR to physicians and assessing their awareness improved the uptake of screening for DR. Use of a referral slip for communication between an ophthalmologist and physicians was an effective strategy to change the behavior of referring physicians [8-17].

Health education intervention could be a low-cost solution to improve the awareness, access, utilization of retinal health care services, but this is an understudied topic in Nepal. Working closely with the stakeholders (health care professionals), this study will evaluate the role of health education interventions (which are already validated in other low-income settings) to reduce the burden of DR in Nepal.

The strength of our study is that it will be one of the first in Nepal that includes health care professionals involved in DM management and strengthens the referral for DR screening.

Because of COVID-19 restrictions, the number of selected health personnel participating in health education could reduce. We also do not have a control hospital to compare our intervention and the effect of the referral pathway between 2 hospitals, which could limit our study’s generalizability. We need further studies to understand barriers faced by health personnel on the referral process and reasons for delays, if any.

